### **3. Resources**

This study consists of four stages: initial assessment (stage 1), intervention (stage 2), short-term follow-up assessment (stage 3), and one-year follow-up assessment (stage 4). At Stages 1, 3, and 4, data will be captured from the participating parent(s) and their child.

Direct child assessments focus on gaining an understanding of the child's autism severity and cognitive ability. A trained member of the research team will administer these assessments within a 1:1 setting. At Stage 4, additional assessments will be included to address school-related skills.

Parent completed assessments consist of a series of standardised questionnaires made available online via REDCap Survey.

*Note.* Three of these assessments are administered by our partner organisation (AEIOU) as part of their existing intake assessments (marked with an asterisk below). As such, these will not be administered at Stage 1 for those participants recruited via AEIOU.

#### **Direct Child Assessments**

Autism severity: The *Autism Diagnostic Observation Schedule (ADOS-2)\** will be used to measure autism severity. Trained members of our research team will administer this at Stage 1, 3 and 4. Although originally designed as a diagnostic assessment, the ADOS-2 is commonly used in research as a quantitative measurement of autism severity with good reliability and validity. It is considered the gold standard assessment of autism.

The ADOS-2 consists of a series of social activities (or 'presses') designed to elicit behaviours directly relevant to the diagnosis of autism. There are five modules, each tailored to a specific developmental level and/or chronological age. The most appropriate module will be selected on a child-by-child basis. Given the age of the children (4- to 5-years), this is likely to be module 1 or 2. Each module can be administered in 40- to 60-minutes. Social activities included in this assessment consist of structured and unstructured activities, such as make-believe play using a series of age-appropriate items, responsiveness to social prompts (e.g. name, eye gaze and pointed), and

construction puzzles. As per the ADOS-2 manual, a parent will accompany children completing Module 1 or 2.

When coding and scoring the ADOS-2, it is useful to have access to video footage of the assessment. As such, parents will be asked to provide consent for their child to be video-recorded while completing the ADOS-2.

Cognitive ability: The *Mullen Scales of Early Learning (MSEL)*\* is a well-established, standardised measure of ability for children age 0-68 months. This will be used to measure child ability (visual reception, receptive language, expressive language, fine motor and gross motor) and provide a Developmental Quotient (DQ). The reliability and validity of the MSEL has been assessed in young children with autism and is commonly used as both a descriptive and outcome measure in this population. Trained members of our research team will administer this assessment at Stage 1, 3 and 4.

School-related skills: We are developing a series of measures to assess children's school-related abilities. These focus on abilities such as school connectedness, motivation, engagement, study skills, socialisation and academic self-concept. These tasks will be developed during 2020. Once finalised, a modification form will be submitted for the inclusion of these measures at Stage 4 of the current study.

### **Parent Completed Questionnaires**

- Preschool Anxiety Scale Revised (PAS-R)
- Anxiety Scale for Children with Autism Spectrum Disorder (ASC-ASD)
- Intolerance of Uncertainty Scale (IUS-P)
- Vineland Adaptive Behaviour Scales 3rd Edition (VABS-3)\*
- Repetitive Behaviour Scale – Early Childhood (RBS-EC)
- Depression Anxiety Stress Scales (DASS)
- Children's Anxiety Life Interference Scale (CALIS)
- Responses to Uncertainty and Low Environmental Structure questionnaire (RULES)
- Social Communication Questionnaire (SCQ; a measure of autism symptoms)
- Short Sensory Profile II (SSPII)
- As with the direct child assessments, we will develop a series of questionnaires to assess parents' perceptions of their child's school-related skills (e.g., motivation, engagement, school connectedness, study skills, socialisation and academic self-concept). These questionnaires will be submitted as a modification and, subject to ethical approval, will be implemented during Stage 4 of the study in 2021.

### **Additional Resources**

- Clinician and parent manuals for the Cool Little Kids (modified for Autism) program. This modified version has been piloted and was found to be acceptable by the participating parents (GU Ref No: 2019/624).

The funding source for this project is ARC LP180100318

#### **4. Background**

**Research Program Structure:** This study forms part of a nested program. The overarching aim is to investigate how anxiety, a commonly occurring condition in autism, impacts attitudes and behaviours that facilitate students' participation in, and ability to benefit from, academic instruction in the classroom. The current study forms the **first phase** of this nested program.

As outlined in the successful Linkage Project grant application, the current study will compare the anxiety levels of two groups of 4- to 5-year-old children with autism: those whose parents have completed the modified Cool Little Kids (CLK) intervention and those that have not. This will likely result in an overall group of children who have a range of anxiety levels; this is of interest in phase two (see below). The randomised control trial method used to allocate parents to the intervention and control groups will allow us to address a secondary aim: Is the modified CLK program able to reduce/prevent anxiety in children with autism? Although a larger scale RCT would be necessary to confidently demonstrate efficacy, the current study involving 64 families will provide important insights into the possible benefits of the intervention.

Ethical approval for the **second phase** of this study will be sought in 2020 from Griffith University and the necessary governing bodies (e.g. Brisbane Catholic Education, Education QLD). Parents who participated in phase one will be invited to take part in phase two. Data collected in phase two will include the teacher's perspective on the child's academic functioning (e.g. reading, mathematics and critical thinking) and academic enablers (e.g. motivation, engagement, interpersonal skills and study skills) within the first 6-months of formal schooling. By combining the data from phase one and two, we can determine whether moderating anxiety in children with autism is associated with academic enablers. This will allow our overarching research questions to be addressed:

1. Is there evidence that anxiety is associated with academic enablers in children with autism?
2. Does anxiety mediate the relationship between autism and academic enablers in children with autism?

**Background Literature:** Anxiety disorders are the most common form of mental disorder in young people, affecting around 7% of Australian youth (Lawrence et al., 2015). These disorders are even more common in children with autism, affecting up to 40% of the population (van Steensel & Heeman, 2017) with an even larger number showing sub-clinical levels of elevated anxiety (Vasa et al., 2013).

Our latest research suggests that children with autism may begin to experience the early signs of anxiety before they even start school. An extensive literature has demonstrated the efficacy of skills-based intervention programs to reduce heightened anxiety among children as young as 3 years of age (Mychailyszyn, 2017). One such program is Cool Little Kids (CLK), which has demonstrated excellent outcomes in the reduction of anxiety among preschool-aged children. Parallel research has shown similar reductions in anxiety among children who are comorbid for anxiety and autism (Mychailyszyn, 2017; Ung et al., 2015). The core treatment strategy in the CLK program is in vivo exposure, which primarily works via

extinction to shift expectations of threat (Craske et al., 2008). In a recent analysis, CLK was found to lead to reductions in anxiety among a group of preschool-aged children with comorbid autism (Craske et al., 2008). Although CLK has shown promise in reducing anxiety among young children with autism, its processes focus primarily on one mechanism of anxiety, threat expectancy. In addition to heightened threat expectancy, an additional key mechanism in the maintenance of anxiety is a reduced ability to tolerate uncertainty (intolerance of uncertainty (IU); Carleton et al., 2010). High levels of IU are likely to be especially pertinent to children with autism. More complete reduction in anxiety might therefore be achieved by incorporating processes that reduce IU, given its key role in the expression of anxiety among children with autism. Modifying the CLK program by incorporating processes to reduce IU should thus allow greater reduction in anxiety among children with autism.

We are currently piloting such a modified version of the program with a small group of parents of children with autism ( $n = 4$ ; GU Ref No: 2019/624). The parents have reported positive feedback on this program during the intervention sessions. The current study aims to determine whether the intervention is able to assist in reducing children's anxiety levels= (as planned as part of the ARC Linkage project to investigate the role of anxiety in the successful development of academic enablers in children with autism). The implementation of this trial will allow the following questions to be addressed:

1. Does the modified CLK program lead to a reduction in the levels of anxiety experienced by young children with autism?
2. Is participation in the modified CLK program associated with lower levels of anxiety post-intervention, compared to children in a control group (i.e. whose parents did not complete the program)?

Drawing upon the initial findings of the CLK and CUES programs, it is hypothesised that parent participation in the modified CLK program will be associated with a reduction in children's anxiety levels from the initial assessments to the follow-up assessments. It is further predicted that children whose parents participated in the modified CLK program will demonstrate lower levels of anxiety post-intervention, than those children in the control condition (i.e., whose parents did not participate in the program). The primary outcome of this study is to provide preliminary evidence regarding whether the modified CLK program can reduce (or prevent) anxiety in children with autism. It will also establish children's anxiety levels in pre-school which will be informative in phase two (should parents consent to their continuing participation).

## **5. Project Description**

### **Setting**

The intervention will be conducted at Griffith University campuses across Queensland or AEIOU Foundation centres (Gold Coast, Logan, Nathan, Camira, Bray Park, Sunshine Coast, and Toowoomba). These locations have training/meeting rooms ideal for the purpose. Parents will be invited to attend the research sessions at a geographically convenient AEIOU or Griffith University location. Although AEIOU facilities may be used for the intervention, no AEIOU personnel will be present or involved in running the intervention.

### Methodological Approach

We will aim to recruit 64 parents of young children with autism (aged 4- to 5-years-old) through social media (Griffith University Autism Centre of Excellence Facebook page) and early intervention centres operated by our research partner, AEIOU Foundation. AEIOU centres are accessed by up to 280 children annually.

Following a randomised control trial (RCT) method, parents will be randomly allocated to one of two conditions: intervention (whereby parents will participate in all stages of the study, including the modified CLK program) and control (in which parents will complete the initial and both follow-up assessment points but not engage in the CLK program). This design allows comparisons to be made between the two groups, which will assist in determining whether the intervention was successful in reducing (or preventing) anxiety in young children with autism, or whether any reduction (or maintenance) simply reflects a natural change due to general development.

Two alternative procedures were considered, yet were both dismissed due to methodological limitations:

- 1) Wait list control: The modified CLK program is aimed at young children (3- to 6-years; Rapee, Kennedy, Ingram, Edwards, & Sweeney, 2005), thus upon completion of the study the participating children would exceed the target age group for the intervention.
- 2) Offering an alternative intervention to the control group: This technique makes it difficult to determine if any differences between the two groups observed post-intervention is a result of the CLK program or the alternative intervention completed by the control group.

It is worth noting that this is the first trial of this modified CLK intervention, so its efficacy as an early intervention for anxiety in autism is unknown. Using this RCT design (i.e. intervention vs. control) allows us to be relatively certain that any post-intervention differences in anxiety level between the two groups are a result of the intervention itself. This type of clear-cut information is vital, as it will provide preliminary evidence of the efficacy of this program, and therefore whether it would be beneficial for future research to conduct a full-scale trial into its utility.

To determine group allocation, each participating family on the database will be allocated a random number via a random number generator. This will then be used to evenly distribute the participants across the two conditions, with those assigned an odd number placed in the intervention group ( $n = 32$ ), and even numbers placed in the control group ( $n = 32$ ).

All participants, regardless of their group allocation, will complete the measures listed in Section 3 at Stage 1 (initial assessments), Stage 3 (short-term follow-up) and Stage 4 (one-year follow-up). The longitudinal nature of this study allows for us to determine the short-term and longer-term effects of the CLK program on the anxiety levels of children with autism. We are also able to examine whether participation in this intervention had any impact on the more distal constructs of, for example, maternal stress (DASS).

Participants will be recruited and assessed in three waves:

1. Beginning January 2020: Recruitment will focus on social media
2. Beginning February 2020: Recruitment via social media and AEIOU
3. Beginning June 2020: Recruitment via social media and AEIOU

For each wave, participation will begin with the completion of the initial assessments (see Section 3), followed by the modified CLK intervention for those in the intervention group (administered as per the manual), short-term follow-up assessments (within two months of CLK program completion) and long-term follow-up assessments (one-year later). The initial three stages of the study will occur over a 5- to 6-month time frame, with the final follow-up assessments occurring one year later.

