#### Procedure after consent is given

Upon obtaining consent, the postdoctoral research fellow / project manager ([name]) will contact consenting parents and provide a link to the online questionnaires. Parents who complete the initial assessments will be advised of their randomly allocated group membership (intervention vs. control). Those in the intervention group will be asked to select a parent group at a convenient location and times for them. All parents will be reminded of the contact details for the research team.

Although parents have provided their informed consent to participate in the research, their children will be asked to provide their assent (where possible) prior to completing the direct child assessments. Given that the verbal ability of some children may be relatively low, their vocalisations and physical behaviours will be taken into consideration when determining their assent. The child's parent(s) will also be present during these assessments, so can assist in interpreting the child's behaviours. At all times, the child's verbal and non-verbal behaviours will be observed. If at any point either the researcher or child's parent feel that the child would like to stop or have a break, the researcher will respond accordingly by either discontinuing or pausing the assessment. Additionally, children with autism often communicate using picture communication symbols. Where appropriate, we will make a "break" symbol available, so the child is able to pause/stop the assessments by presenting this symbol.

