#### Research Activities

Participants in the intervention group will attend a parent-mediated, group-based intervention designed to prevent/reduce anxiety in their children with autism. The intervention consists of six two-hour sessions spaced over a school term. The intervention has a clinician manual and a parent workbook and parents are asked to undertake some homework activities between sessions.

Parents and children will also participate in initial and follow-up assessments (stage 1, 3 and 4) that will take place approximately two weeks prior to the intervention, two weeks following the intervention, and one-year later. Children recruited via AEIOU will only require the follow-up assessments (stage 3 and 4) as they will have already completed the ADOS and MSEL during their AEIOU intake assessment. All stage 1, 2 and 3 activities will be completed by December 2020; the final follow-up will be conducted the following year (2021).

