#### Data Collection/Gathering

**Parents:** All parents will be asked to complete questionnaires at Stage 1, 3, and 4 (initial assessments, short-term follow-up and one-year follow-up). These questionnaires will be administered using REDCap so they can be completed online. The questionnaires ask parents to report on their child's anxiety, intolerance of uncertainty, repetitive behaviours, the impact anxiety may have on daily life, and other relevant constructs. Note that at Stage 1, parents recruited via AEIOU will not have to complete the Vineland caregiver questionnaire as this is administered as part of the AEIOU intake procedure.

At Stage 4, additional parent questionnaires will be added to assess their child's school-related skills (subject to approval of modification request; see Section 3). All parents will be invited to answer these items. We will provide parents with additional details regarding Stage 4 assessments closer to the time.

The standardised questionnaires completed by the parents are as follows:

- Preschool Anxiety Scale Revised (PAS-R)
- Anxiety Scale for Children with Autism Spectrum Disorder (ASC-ASD)
- Intolerance of Uncertainty Scale (IUS-P)
- Vineland Adaptive Behaviour Scales 3rd Edition (VABS-3)\*
- Repetitive Behaviour Scale – Early Childhood (RBS-EC)
- Depression Anxiety Stress Scales (DASS)
- Children's Anxiety Life Interference Scale (CALIS)
- Responses to Uncertainty and Low Environmental Structure questionnaire (RULES)
- Short Sensory Profile II
- Social Communication Questionnaire (SCQ; a measure of autism symptoms)

In addition, parents recruited via an early-intervention centre will be asked to consent to the sharing of assessment data already collected by their child's AEIOU Foundation centre. Sharing of these data will be beneficial in describing the participant group and will save repeating these assessments unnecessarily.

Specifically, the following assessment data will be requested:

- Autism Diagnostic Observation Scale-Second Edition
- Mullen Early Learning Scales
- Vineland Adaptive Behaviour Scale- Third Edition

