#### Outcome measures (see attached questionnaire pack)

- Preschool Anxiety Scale Revised (PAS-R)
- Anxiety Scale for Children with Autism Spectrum Disorder (ASC-ASD)
- Intolerance of Uncertainty Scale (IUS-P)
- Vineland Adaptive Behaviour Scales 3rd Edition (VABS-3)\*
- Repetitive Behaviour Scale – Early Childhood (RBS-EC)
- Depression Anxiety Stress Scales (DASS)
- Children's Anxiety Life Interference Scale (CALIS)
- Responses to Uncertainty and Low Environmental Structure questionnaire (RULES)
- Social Communication Questionnaire (SCQ; a measure of autism symptoms)
- Short Sensory Profile II (SSPII)
- School-related skills: These tasks are currently being developed and will be submitted as a modification prior to their implementation during 2021.

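### The protocol treats post-intervention anxiety differences as near-certain effects of the programme, but every Stage 3 and Stage 4 anxiety score comes from a parent who knows the allocated arm

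*Protocol*

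**What the plan says.** Section 5, Methodological Approach, justifies the choice of a randomised no-programme control. It says this design "allows us to be relatively certain that any post-intervention differences in anxiety level between the two groups are a result of the intervention itself", describes the resulting information as clear-cut, and says it will show whether a full-scale trial would be worthwhile.

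The features that bear on that claim are stated elsewhere in the protocol:

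- **Who rates anxiety.** Data Collection/Gathering: "The questionnaires ask parents to report on their child's anxiety, intolerance of uncertainty, repetitive behaviours, the impact anxiety may have on daily life". The child anxiety instruments (PAS-R, ASC-ASD, CALIS) all appear in the list of parent questionnaires.
- **What researchers assess directly.** Section 3: "Direct child assessments focus on gaining an understanding of the child's autism severity and cognitive ability". School-related skills are added at Stage 4. Anxiety is not among the direct assessments.
- **When parents learn their arm.** Procedure after consent is given: "Parents who complete the initial assessments will be advised of their randomly allocated group membership (intervention vs. control").
- **What the intervention arm receives.** Research Activities: "The intervention consists of six two-hour sessions spaced over a school term", with homework between sessions. The parents attend.
- **What the control arm receives.** Methodological Approach: "control (in which parents will complete the initial and both follow-up assessment points but not engage in the CLK program").

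**The concern.** The quoted sentence is about differences in the child's anxiety, but what the trial observes after the intervention is the parent's report of it. At Stages 3 and 4 that report comes from someone who knows the arm. In the intervention arm it also comes from someone who has just been taught about anxiety and how to manage it. Section 6 (Return of results) expects such learning: it says the report and participation in the intervention help parents learn more about anxiety and its management. Only one arm takes part in the intervention.

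A between-arm difference can therefore contain three things: a change in the child, the parent's expectation of benefit, and a change in the standard by which the parent rates. The protocol attributes the total to the first. A difference made up wholly of the other two would be read as evidence of efficacy and would support a full-scale trial.

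**Working it through.** **1. What the design rules out and what it leaves**

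| Alternative explanation | Removed by design? | Basis in the protocol |
|---|---|---|
| Selection into the arms | Yes | Random allocation |
| Natural development | Yes | Concurrent randomised control, as Methodological Approach says |
| Parental expectancy | No | Arm disclosed after Stage 1; anxiety rated by parents |
| Changed rating standard in trained parents | No | The rater attends the sessions in one arm only |

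Stage 1 questionnaires are completed before the arm is disclosed, so those scores are not affected. The affected scores are those at Stages 3 and 4, which are the ones the quoted sentence is about.

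**2. Does any anxiety measure escape the problem?** PAS-R, ASC-ASD and CALIS are all parent-completed. The researcher-administered ADOS-2 and MSEL measure autism severity and cognitive ability. No masked, clinician or independent anxiety rating is described.

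**3. Size, as an illustration**

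The protocol gives 32 per arm. It gives no alpha, effect size, SD, power or dropout, so there is no stated figure to reproduce. Assumptions added here: two-sided 5% t-test, scores in SD units, no dropout, no true change in the child, and a reporting shift of b SD in favour of the programme.

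- Standard error of the difference: √(2/32) = 0.25 SD.
- Degrees of freedom: 32 + 32 − 2 = 62; critical value 2.00.
- Noncentrality: b / 0.25.
- Rejection probability: P(|T| > 2.00), with T noncentral t on 62 df.

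| Assumed shift b (SD) | Noncentrality | P(significant) |
|---|---|---|
| 0 | 0 | 5.0% |
| 0.2 | 0.8 | 12.4% |
| 0.3 | 1.2 | 21.9% |
| 0.4 | 1.6 | 35.0% |

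Nearly all of these rejections favour the programme: at 0.2 SD, 12.1 of the 12.4 percentage points. Counting only results in that direction, the reference rate is 2.5% rather than 5%. A normal approximation gives nearly the same two-sided values: 12.6%, 22.4% and 36.0%.

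**4. Would a larger trial cure it?** No. With 128 per arm the standard error is √(2/128) = 0.125 SD. A shift of 0.3 SD then has noncentrality 0.3 / 0.125 = 2.4 and is significant in about 67% of trials. Size makes the bias easier to detect as an apparent effect; it does not remove it.

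**5. Could the SCQ reveal a reporting shift?** The SCQ is parent-rated and is listed among the outcome measures ("Social Communication Questionnaire (SCQ; a measure of autism symptoms"). For the same shifts and the same 32 per arm, the chance of detecting a shift on it is the column above: 12% to 35%, so it would be missed 65% to 88% of the time. The 95% interval is about ±2.00 × 0.25 = ±0.50 SD. A shift confined to how parents rate anxiety need not appear on an autism-symptom scale at all.

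**The case against.** The strongest reply is that the sentence is hedged and has a narrow purpose. It says relatively certain, the next sentence speaks of preliminary evidence, and Section 4 says a larger trial would be needed to demonstrate efficacy with confidence. The paragraph explains why a concurrent randomised control was preferred to two alternatives, and against natural development it is right. Parents of 4- to 5-year-olds cannot be masked to attending a programme, and parent report is a practical choice when some children have limited verbal ability.

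Much of that stands. However, the hedges concern sample size and stage of evidence. None mentions rating by unmasked parents, and the clear-cut wording restores the strong reading. That masking is impossible is a reason to state the limit, not to claim its absence.

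Several stronger readings are tempting, and the documents do not support them:

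- **That all anxiety scores are unmasked.** Stage 1 scores precede disclosure.
- **That a no-programme control is itself a fault.** Programme versus no programme is a legitimate contrast, and group contact is part of a group programme. The protocol considered an alternative-intervention control and gave its reason for rejecting it. Unequal contact matters only if the claim is about the programme's specific content.
- **That a formal go/no-go rule would be corrupted.** There is none. The protocol says only that the result informs whether a full-scale trial would be beneficial.
- **That an SCQ comparison would settle the matter.** It has little power here and could miss an anxiety-specific shift. Nothing in the protocol says the programme should leave the SCQ unchanged.

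**Conclusion.** The point holds as a limit on inference: the protocol claims a property that its design lacks. A Stage 3 or Stage 4 difference is a difference in parent-reported anxiety between programme and no programme, and it cannot be separated from expectancy or a change in reporting.

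The 12% to 35% range rests on assumed shifts of 0.2 to 0.4 SD, a two-sided 5% t-test, 32 per arm with complete follow-up, and no true effect. A reader might take it as the trial's actual false-positive rate. It is not: the documents give no information on whether a shift occurs, how large it is or in which direction. Training could also make parents notice more anxiety, which would hide a real benefit. The conclusion does not depend on the range; it follows from who rates, what they know and what they have been taught.

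The correction is worth making because it changes what the trial may conclude. It does not make the trial or its comparison invalid.

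**What to change.** 1. In Methodological Approach, replace the quoted sentence with wording such as: *A between-group difference is an effect of the programme, compared with no programme, on parent-reported anxiety; because parents are not masked, it cannot be separated from expectancy or a change in parental reporting.*
2. Delete the clear-cut description that follows it.
3. Carry the same limit into the statement that the result informs whether a full-scale trial would be beneficial. Say there that a larger trial using the same raters would not remove it.
4. Do not rely on an SCQ comparison to resolve the question. If it is reported, label it an exploratory, one-way check: a similar shift would be a warning sign, but a null result must not be read as excluding reporting bias.

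The cost is a few sentences of protocol text and a more modest claim. No assessment, rater, arm or participant is added.

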We will also provide parents with confidential research reports; one after Stage 1 (for those recruited through social media only) and after Stages 3 and Stage 4 for all participants). These will detail their child's level of IQ and adaptive functioning and can be shared with anyone they wish as it may assist in providing others with further information on their child's ability and skills.

Sample management: Parents who consent to participate based on the first social-media advert will be allocated to wave one (until this reaches capacity), with any additional parents allocated to wave two and three as needed. For wave two, invitations will be circulated to AEIOU parents (and social media if necessary). In the unlikely event that all invitations are accepted, these families will be divided across wave two and three. If only a subsample accepts the invitation, they will be allocated to wave two (until this reaches capacity), with any additional parents allocated to wave three. The AEIOU uptake rate observed here will give us a better idea of the number of potential families to circulate the study information to for the third wave.

Any parents who accept the invitation in the third round of recruitment will be allocated to wave three.

Given our staged recruitment strategy across multiple waves, it is unlikely that a large number of additional parents will wish to participate. The number of parents approached at each wave can be adjusted to reflect the number of parents who have already consented to the project. We anticipate that the three waves may not be equal in size and this has been factored into the study design and therapist availability to run groups.

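### The odd/even allocation rule as written does not secure the stated 32/32 split, and no balance within wave or recruitment source is described

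*Protocol*

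**What the plan says.** Under Methodological Approach, the protocol aims for 64 families and says that "each participating family on the database will be allocated a random number via a random number generator". The purpose and the rule are given together: "evenly distribute the participants across the two conditions, with those assigned an odd number placed in the intervention group". Families whose number is even form the control arm, and each arm is stated to have n = 32. The section does not state the range of the numbers, whether a number can repeat, or whether they are drawn once for the trial or afresh for each wave.

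The same section says: "Participants will be recruited and assessed in three waves". They start in January, February and June 2020. The first is described as "Beginning January 2020: Recruitment will focus on social media"; the other two recruit from social media and AEIOU centres. The sample management paragraph adds: "We anticipate that the three waves may not be equal in size and this has been factored into the study design", and the sentence goes on to mention therapist availability. Under Procedure after consent is given, parents learn their group once they have completed the initial assessments.

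**The concern.** On its plain reading, the parity of a generated random number is a separate coin toss for each family. A series of coin tosses does not produce fixed arm sizes, so the mechanism and the stated n = 32 per arm do not fit together. This is not a detail that can wait for a statistical analysis plan. The protocol has chosen and written down an allocation rule, and it rests its confidence in attributing differences to the intervention on the randomised design.

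The second issue is balance over time and source. Waves 2 and 3 draw partly on children attending early-intervention centres, whose Stage 1 ADOS-2, MSEL and Vineland data come from AEIOU intake. If most families in one wave fell by chance into one arm, the arms would differ in calendar period and probably in the mix of sources. In a trial of 64 families such an accident is not rare, and nothing described in the protocol limits it.

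**Working it through.** **Inputs from the protocol.** N = 64; 1:1 allocation, 32 per arm; three waves; two sources. Wave and source sizes are not given, so they are assumed below.

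**1. The stated split under independent draws.** Arm size X follows Binomial(64, 0.5), with SD = √(64 × 0.5 × 0.5) = 4.

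- P(X = 32) = C(64, 32) / 2^64 = 0.099
- P(28/36 or worse) = 2 × P(X ≥ 36) = 0.382
- P(26/38 or worse) = 2 × P(X ≥ 38) = 0.169
- P(24/40 or worse) = 2 × P(X ≥ 40) = 0.060

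The stated 32/32 is therefore not reproduced by the rule, except about one time in ten.

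**2. The stated split if numbers 1 to 64 are used once each.** There are 32 odd and 32 even numbers, so the split is exactly 32/32. This needs one pool of numbers spanning all three waves, because wave 1 families learn their group before wave 3 has been recruited. It also needs exactly 64 families to be allocated.

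**3. Balance within waves.** The event is that at least one wave has two thirds or more of its families in one arm (rounded up to whole families). For independent draws the formula is 1 − Π(1 − p_w), with p_w = 2 × P(Binomial(m, 0.5) ≥ ⌈2m/3⌉) for a wave of m families. For 21/21/22 the thresholds are 14, 14 and 15, and p_w = 0.189, 0.189 and 0.134. The result is 1 − 0.811 × 0.811 × 0.866 = 0.43. For numbers used once, all allocations totalling 32 were enumerated.

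| Assumed wave sizes | Independent draws | Numbers 1–64 used once |
|---|---|---|
| 21/21/22 | 0.43 | 0.22 |
| 12/26/26 | 0.48 | 0.35 |
| 10/22/32 | 0.46 | 0.34 |

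**4. Balance within a source.** The event is a split of 62.5% or worse (rounded up) among the families from one source.

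| Assumed families in the source | Independent draws | Numbers 1–64 used once |
|---|---|---|
| 16 | 0.45 | 0.39 |
| 20 | 0.26 | 0.18 |
| 32 | 0.22 | 0.08 |

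**5. Power cost of unequal arms.** Power = Φ(d × √(n₁n₂/(n₁+n₂)) − 1.96), two-sided 0.05, with an assumed standardised difference d = 0.7 (the protocol gives none).

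- 32/32: Φ(0.7 × √16 − 1.96) = 0.800
- 28/36: Φ(0.7 × √15.75 − 1.96) = 0.793
- 24/40: Φ(0.7 × √15 − 1.96) = 0.774

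**The case against.** The best defence is that the sentence can be read as restricted randomisation. The stated aim of an even spread and the two n = 32 figures fit numbers 1 to 64 used once each, and every overall-imbalance figure then disappears. This stands as a possible reading, and for that reason it would be wrong to infer that the rule cannot give 32/32. Even independent draws give it about 10% of the time. But the text does not state that scheme, and it leaves a third one open: numbering afresh within each wave, which would balance waves but not sources. Of these three readings, none controls source, and only the unstated per-wave numbering controls wave.

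Three further points on the other side are sound.

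- A reader might infer that the comparison is biased or confounded. The documents do not support that. Simple randomisation is valid, chance imbalance is not systematic, and wave and source are known and can be adjusted for. The difference in baseline source affects only ADOS-2, MSEL and Vineland. The anxiety questionnaires (PAS-R, ASC-ASD, CALIS) are completed in the same way by families from both sources.
- A reader might infer that staff would override the numbers by hand to reach 32 per arm. No such step is described.
- The protocol expects unequal waves and says it has allowed for them. That statement concerns wave size and therapist availability rather than balance between arms, but it does show that filling the parent groups was considered.

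The trial is also presented as preliminary, which limits how much weight the point should carry.

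**Conclusion.** The point holds as a mismatch between the allocation mechanism and the arm sizes it is said to produce, together with the absence of any described balance by wave or source. If draws are independent, 32/32 occurs about 10% of the time, and 28/36 or worse about 38%. Under the three wave-size patterns assumed, the chance of at least one wave with two thirds or more in one arm is 43–48%, or 22–35% if numbers are used once. These wave figures show the order of magnitude only, because the protocol gives no sizes.

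The statistical harm is modest. Power falls from 0.800 to 0.774 even at 24/40, for the assumed difference of 0.7, and validity is not threatened. This should be fixed because the remedy is nearly free and must precede allocation, not because the trial would otherwise fail.

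**What to change.** Replace the odd/even rule with a computer-generated 1:1 permuted-block list stratified by wave, prepared before wave 1 and concealed from those who recruit and assess. State the arm sizes as approximately 32 per arm.

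Add recruitment source as a stratum only if the strata would not become too small. If wave 1 is social media only, source within wave gives 1 + 2 + 2 = 5 strata, or about 64/5 ≈ 13 families each. Whether the analysis adjusts for wave can be left to the statistical analysis plan.

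The cost is a wording change and about an hour to generate the list, with no extra families or staff. The small downside is that an unfilled block can leave a difference of up to half a block in each wave. An exact 32/32 is therefore still not guaranteed, and the arms may differ by a few families.
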